## Methods

### Pilot study

Four physiotherapists in private practice (including the researcher) will be the treating physiotherapists. All the physiotherapists are qualified manual therapists with knowledge of neural mobilisations. All participating physiotherapists will take part in a training workshop run by the researcher. The training workshop will consist of: training of the application of neural mobilisation along the course of the nerve, protocol for treatment groups, outcomes measures, baseline measures as well as patient screening.

The inter- and intra-rater reliability of the researcher and the research assistant was established for the ULNDT1. Inter-class correlation coefficient was good at 0.85, (95% CI 0.66-1.06). Intra-class correlation coefficient for physiotherapist 1: 0.85, (9 5% CI 0.64 -1.06) and for physiotherapist 2: 0.70 (95% CI 0.31- 1.09) which was acceptable.

### Initial assessment

Patients presenting at participating physiotherapy practices with neck and arm pain will be screened for inclusion into the study. Suitable candidates will receive a full musculoskeletal examination to confirm that they comply with the criteria for cervico-brachial pain as described above [8]. They will then complete the questionnaires as discussed.

Physical examination will include the ULNDT1. The test will be done as described above [33]. The range of ULNDT1 will be measured using a standard goniometer to measure the range of elbow extension [57]. The examination section of the DN4, that is; testing for hypoesthesia to touch, and prick and pain caused by brushing will be done at baseline, six months and 12 months. Neural conduction tests of sensation, muscle power and reflexes will be done according to Petty & Moore [58] at six and 12 months. They will also be asked to complete a demographic questionnaire on age, gender, duration of symptoms, previous neck pain, injury or insidious onset, education, occupation, sport, presence of headache or dizziness and indicate the area of pain on a body chart.

### Randomisation

Block Randomisation with a 2:1 ratio in blocks of 6 will be done [59, 60]. According to Moher et al. [61] an unequal randomisation is ideal for smaller randomised controlled trials and multicentre trials [61]. Randomisation will be done using a computer random generator [62]. An independent research assistant, naïve to study content, will be contacted by telephone. This research assistant will give a patient number sequentially and treatment (group) allocation to participating physiotherapists after all baseline measurements has been done.

Physiotherapists will receive an envelope with the patient information leaflet, consent form, treatment recording sheet and all questionnaires. Group allocation will not be visible and the research assistant doing follow up measurements will be blinded to group allocation. Treatment recording sheets will only be collected at the end of the data collection period. The treatment sheets will be used to assess whether treatment allocation was followed, number of treatment sessions and to screen for any adverse events due to treatment.

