**Methods:**

A randomised controlled trial will be used to establish the effect of neural mobilisation on the pain, function and quality of life of patients with cervico-brachial pain. Patients will be recruited in four physiotherapy private practices and randomly assigned to usual care or usual care plus neural mobilisation.

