### Sample size

Primarily this study sets out to assess whether, 6 weeks after onset of treatment the Numerical Pain Rating Scale NPRS score in the intervention group is reduced compared to the UC group. A blocked 2:1 ratio randomisation for intervention to usual care will be done using a computer generated random number list. A sample size of 68:34 i.e. a total sample of 102 patients will have 90% power to detect a clinically relevant increase of 2 for the change from baseline at six weeks in the NPRS score. A standard deviation of 2.05 was assumed as derived from the effect size reported by Bolton and Wilkinson [42]. The standard deviation was furthermore inflated by √2 since change from baseline is of interest. A dropout rate of 15 – 20% was assumed. One-sided testing will be done at the 0.05 level of significance. (nQuery advisor 7).

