### Data analysis

The data summary will employ descriptive statistics, means, standard deviations and 95% confidence intervals and will be reported by study group (intervention & standard care) for the NPRS, PSFS and EQ-5D. Catastrophising (yes & no) and neuropathic pain (yes & no) will be summarised using frequencies, percentages, cross tables and 95% confidence intervals.

Two treatment groups will be compared with respect to the change from baseline at six weeks in the NPRS, PSFS and EQ-5D scores using an analysis of covariance (ANCOVA) with baseline scores, catastrophising (yes & no) and neuropathic pain (yes & no) as covariates. For the total assessment period of 12 months the interaction between visits and treatment will be assessed with respect to NPRS, PSFS and EQ-5D scores in a linear mixed model analysis. Testing will be done at the 0.05 level of significance. For all data description and analyses an intention-to-treat analysis will be performed.

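### A single fixed block size of 6, presumably known to at least one recruiting therapist, and a six-week ANCOVA that leaves out practice: both are cheap to improve

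*Protocol article*

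**What the plan says.** The Sample size section announces the scheme: "A blocked 2:1 ratio randomisation for intervention to usual care will be done using a computer generated random number list". The Randomisation section fixes the block: "Block Randomisation with a 2:1 ratio in blocks of 6 will be done". It then describes release of the assignment: "An independent research assistant, naïve to study content, will be contacted by telephone", and "This research assistant will give a patient number sequentially and treatment (group) allocation to participating physiotherapists after all baseline measurements has been done". The article does not say whether there is one list or one per practice.

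On who recruits and treats, the abstract says "Patients will be recruited in four physiotherapy private practices and randomly assigned to usual care or usual care plus neural mobilisation", and the Pilot study section says "Four physiotherapists in private practice (including the researcher) will be the treating physiotherapists". The same section includes patient screening and baseline measures in these therapists' training. Initial assessment places screening and examination at the practices, and Outcome measures has the treating physiotherapist give the first questionnaires.

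On analysis, the Data analysis section compares six-week change "using an analysis of covariance (ANCOVA) with baseline scores, catastrophising (yes & no) and neuropathic pain (yes & no) as covariates". The 12-month mixed model is described through the visit-by-treatment interaction, with no practice term.

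**The concern.** Two stated choices deserve a second look.

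First, the block size is single and fixed, and people who cannot be blinded to treatment decide who enters. Eligibility rests on clinical judgement (at least five of a set of examination findings). A recruiter who knows the block size and has seen the earlier assignments in a block can sometimes deduce the next one, and could then enrol, delay or decline a borderline patient accordingly. The researcher is one of the four recruiters and can be presumed to know the scheme.

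Second, four therapists in four practices deliver a manual treatment, so outcomes may well differ by practice. The listed covariates do not absorb that variation. If the list does not hold the ratio within practices, chance imbalance by practice adds noise to the treatment comparison.

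**Working it through.** **The plan's own figure.** Inputs from Sample size: difference 2, SD 2.05 × √2 = 2.899, one-sided 0.05, 90% power, 2:1, dropout 15–20%.

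- Usual care: n = (1.6449 + 1.2816)² × 2.899² × (1 + 1/2) / 2² = 8.564 × 8.405 × 0.375 = 26.99, so 27, with 54 on intervention (81 evaluable).
- At 20% dropout: 27 / 0.80 = 33.75, so 34:68 = 102.

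The stated 102 reproduces at 2:1. It is also exactly 17 blocks of 6.

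**Case A: a separate list per practice.** The therapist sees every assignment in the block and knows it holds 4 intervention and 2 usual care. There are 15 arrangements, hence 15 × 6 = 90 positions. An assignment is certain once one arm is used up.

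- Expected number of certain positions per block: 4/(2+1) + 2/(4+1) = 1.333 + 0.400 = 1.733. Over 15 arrangements this is 26 of 90 = 28.9%.
- Guessing the arm with more places left is right in 67 of 90 = 74.4%.
- Always guessing intervention is right in 4/6 = 66.7%. The gain from knowing the block is therefore about 8 points.

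**Case B: one central list.** Simulation of 17 blocks of 6, each patient equally likely to come from any of four practices (an assumption; the article gives no practice sizes). The therapist sees only their own assignments and patient numbers.

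- About 1.5% of assignments are certain, and the best guess is right about 67% of the time, practically the free rate.
- Intervention share within a practice: 95% range about 50–83% around 67%. The gap between the highest and lowest practice has median 19 points and 95th percentile 34 points.

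**Precision lost in Case B without practice in the model.** Let ρ be the intraclass correlation by practice. The documents give none; 0.01–0.10 is assumed. In units of the total variance:

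- unadjusted: (1 − ρ)(1/68 + 1/34) + ρS, where S is the sum over practices of (intervention count/68 − usual-care count/34)², averaging 0.0332 in the simulation;
- adjusted, before the cost of fitting practice: (1 − ρ)(1/68 + 1/34), with 1/68 + 1/34 = 0.0441.

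The ratio is 1 + (0.0332/0.0441) × ρ/(1 − ρ) = 1 + 0.752 ρ/(1 − ρ).

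| ρ | variance ratio | power at 27:54 if practice variance is removed (90.0% otherwise) |
|---|---|---|
| 0.01 | 1.008 | 90.3% |
| 0.05 | 1.040 | 91.3% |
| 0.10 | 1.084 | 92.5% |

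The power column is Φ(2 / [2.899 √(1 − ρ) √(1/27 + 1/54)] − 1.645).

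**Cost of adjusting.** Three practice terms on an unstratified list inflate the adjusted variance by roughly 1/(1 − 3/101) = 1.03. Net of this the ratios are about 1.008/1.03 = 0.98, 1.040/1.03 = 1.01 and 1.084/1.03 = 1.05. On an unstratified list, adjustment thus breaks even near ρ = 0.04. If the list is stratified by practice, most of that cost disappears.

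**The case against.** The strongest reply is that allocation is well protected. An independent assistant releases each assignment by telephone, and only after all baseline measurements. That stands, and it leaves only inference near the end of a block. The sequential numbering and the wording in Sample size point to one central list, under which very little can be inferred.

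Four stronger readings are tempting, and the documents do not support them.

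- *Predictability and imbalance both apply in full.* They largely exclude each other. A list per practice makes blocks visible but keeps each practice near 2:1; a central list does the reverse.
- *All four therapists know the block size.* Neither the listed workshop content nor the therapists' envelope includes the randomisation scheme. Only the researcher can be presumed to know it.
- *The trial is not stratified.* The article is silent, and a condensed article may leave this to the full protocol. The block size and the covariate list, by contrast, are positive statements.
- *2:1 is an error that costs this trial power.* The article reports a cited view that "an unequal randomisation is ideal for smaller randomised controlled trials and multicentre trials". For a fixed total, 2:1 does give 1.125 times the variance of 1:1, but the 102 was sized at 2:1 for 90% power, so that cost is already paid. The ratio is a design preference.

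**Conclusion.** The point holds in a limited form. One fixed block size is stated, at least one recruiting and treating therapist can be presumed to know it, and practice is missing from an explicit covariate list.

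Which consequence follows depends on a fact the article leaves open. With a list per practice, predictability matters and within-practice balance is nearly assured. With one central list, predictability is slight and chance imbalance by practice is the live issue.

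A reader might infer that such imbalance biases the treatment effect by mixing in therapist effects. It does not: under randomisation it is chance, the estimate stays unbiased, and the loss is in precision. That loss is small, about 1–8% of variance, or 0.3–2.5 power points at most, and it rests on the assumed intraclass correlation and equally sized practices. Nothing shows that enrolment would in fact be influenced. This is a worthwhile, inexpensive improvement and no threat to the trial's validity.

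**What to change.** 1. Add practice (four levels) as a fixed effect to the six-week ANCOVA and to the 12-month mixed model, specified before any outcome data are seen by arm.
2. State whether there is one list or one per practice.
3. Have the independent assistant use randomly varied block sizes in multiples of 3, kept out of anything the therapists see. The protection comes from the variation and non-disclosure; a fixed, known block of 3 would be worse than 6 (44.4% certain if fully seen).
4. If recruitment has not begun, stratify the list by practice, so that balance holds and adjustment costs little.

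The cost is a new computer list, one line in each model and three degrees of freedom. If the list stays unstratified and practices differ very little, adjustment may give back about 2–3% of variance. The sample size of 102 and the 2:1 ratio need not change.

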### Outcome measures

The treating physiotherapist will administer the first set of questionnaires. Treatment randomisation will only be done as described above, after initial measures have been taken. All subsequent follow up questionnaires will be administered by a research assistant who will be blinded to group allocation as the follow up questionnaires at three weeks and six weeks will be done telephonically. The primary outcomes are pain (Numeric Pain Rating Scale), function (Patient Specific Functional Scale) and quality of life (EuroQual Instrument). These self-report outcomes will be followed up at three weeks, six weeks, six months and 12 months.

The NPRS will be used to measure the patient’s pain. The NPRS is an 11-point scale where patients are asked to rate their pain as 0 representing “no pain” and 10 “worst pain possible”. In a study comparing three pain measures [42]. Bolton and Wilkinson [42] found the NPRS to be the most responsive pain measure with an effect size of 0.86 [42]. The validity of the NPRS in an acute setting was established by Bijur et al. [43] and is strongly correlated with the visual analogue scale (r = 0.94, 95% Confidence Interval 0.93 – 0.95) [43]. The NPRS is as sensitive to change as the visual analogue scale which is currently considered the “gold standard” [44].

The Patient Specific Functional Scale (PSFS) will be used to measure disability. The PSFS is a self-report measure to rate activity limitation and function. Patients are asked to nominate three to five activities that are difficult to perform and rate them on an 11 point scale where 0 equals “unable to perform activity” and 10 represents “able to perform activity as before”. The scale was initially developed for patients with back pain and validated for patients with neck pain by Westaway et al. [45]. The scale has excellent validity (r = 0.73 - 0.83) when compared to the Neck Disability Index [45]. The test retest reliability coefficient is excellent (ICC = 0.97) [46]. Cleland et al. [47] compared the Neck Disability Index (NDI) and the PSFS in patients with cervical radiculopathy and found that the PSFS was more responsive than the NDI in this population [47]. In their study the test-retest reliability coefficient was good (ICC 0.82). The scale is commonly used in physiotherapy practice [48].

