### Intervention

The American Physical Therapy Association Guidelines [27] as well as the Australian Guidelines [63] both recommend the use of a multimodal intervention comprising of gentle exercise, advice to stay active and cervical mobilisation/manipulation. The usual care (UC) [40] will be given according to these guidelines to ensure that all patients receive evidence based care. No specific mobilisation/ manipulation technique have been shown to be superior to another [64, 28].

The UC will consist of mobilisation of the cervical and thoracic spine, exercises and advice to stay active. As most physiotherapists in South Africa have been Maitland trained, the patients will receive Maitland mobilisation [65] of the cervical and thoracic spine. Exercises will include postural correction, deep neck flexor training according to Falla et al. [66] and strengthening and mobilising exercises using yellow Theraband™ as described by [67]. All study participants will receive advice to stay active [27]. The number of treatments will range between two and a maximum of eight treatments and will be recorded. Patients who have not improved by the sixth treatment or patients who report any adverse events will be referred back to their general practitioners. Patients in the UC group will not receive any neural mobilisations.

The intervention group will receive the NM in addition to UC. The NM used in this study will be done as described by Butler [33], a gentle soft tissue mobilisation of the neural container/interface “along the tract” ([33] pp. 380) of the nerve – directly where the nerve is palpable and indirectly where it lies deeper. The treatment will concentrate on areas where the nerve is mechano-sensitive to palpation and will be done from the hand or elbow (depending on patient’s area of pain) and followed up along the arm, first rib, scalene and into the neck. Mobilisation will first be done in a position where the nerve is relaxed, not provoking any of the patient’s symptoms. Palpation may only provoke minimal symptoms and should disappear as soon as it is stopped. The basic principles of neural mobilisations will be used to progress treatment; that is to commence treatment in the acute phase with the nerve in a neutral, non-tension position and to progress into a more tensioned position as pain and irritability improves [33, 68].

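### The only stated source for adverse events is a treatment sheet kept by therapists who know the allocation, limited to events due to treatment, and the blinded follow-up contacts list no harm item

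*Protocol article*

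**What the plan says.** All references are to the protocol article.

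- **Source and scope.** Under Randomisation: "The treatment sheets will be used to assess whether treatment allocation was followed, number of treatment sessions and to screen for any adverse events due". The last of these uses reads in full: "to screen for any adverse events due to treatment". The same section adds: "Treatment recording sheets will only be collected at the end of the data collection period".
- **Who holds the sheets.** The physiotherapists receive the sheet in the patient's envelope. They are also told the arm: "This research assistant will give a patient number sequentially and treatment (group) allocation to participating physiotherapists". Under Pilot study: "Four physiotherapists in private practice (including the researcher) will be the treating physiotherapists".
- **A second mention of harm.** The Intervention section sends patients who report any adverse event back to their general practitioner. It does not limit this to events caused by treatment, and it does not say where the event is recorded.
- **Treatment and follow-up.** Under Intervention: "The number of treatments will range between two and a maximum of eight treatments and will be recorded". Under Outcome measures: "These self-report outcomes will be followed up at three weeks, six weeks, six months and 12 months".
- **Blinded contact.** Under Outcome measures: "All subsequent follow up questionnaires will be administered by a research assistant who will be blinded to group allocation". The three- and six-week contacts are by telephone. The listed instruments are the NPRS, PSFS and EQ-5D, with the GROC at six weeks. The DN4 and the catastrophising scale are repeated at six and 12 months. No adverse event item is listed.
- **Analysis.** Data analysis compares the arms on NPRS, PSFS and EQ-5D. It states no comparison of adverse events.

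**The concern.** The trial adds a nerve-directed manual technique to usual care. Readers will want to know whether the addition does harm, and will read any adverse event counts by arm whether or not a test is planned. Counts support that reading only if events are sought in the same way in both arms, over the same period, and without a judgement of cause by someone who knows the arm. The stated method secures none of the three. Events that are not asked about during the trial cannot be recovered reliably afterwards.

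**Working it through.** The article gives no figure for harm, so the check is mainly a comparison of sections, with a short illustration of size.

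**1. Does any sample size input depend on harm?** The stated inputs are a difference of 2 NPRS points, SD 2.05 × √2 = 2.899, one-sided 0.05, 90% power, 2:1 allocation and 15–20% dropout.

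- Control n = (1.645 + 1.282)² × 2.899² × (1 + 1/2) / 2² ≈ 27; intervention 54.
- At 20% dropout, 27/0.80 = 33.75, so 34, and 54/0.80 = 67.5, so 68. The total is 102, as stated.

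Harm enters nowhere, so the sample size is untouched.

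**2. Scope.** Randomisation restricts the screen to events due to treatment. Intervention speaks of any adverse event a patient reports. The second set is wider, and no rule says whether events in it but not in the first are recorded.

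**3. Attribution.** Whoever judges cause from these sheets works from the notes of a person who gave the treatment and knows the arm. The judgement need not work alike in both arms. The Intervention section describes a small, transient provocation of symptoms as acceptable during nerve palpation, and usual care has no such category. A therapist could therefore pass over arm symptoms after neural mobilisation as expected, or attribute them more readily to the added technique. Either direction is possible.

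**4. Period.** Sessions number two to eight, and the calendar length of the course is not given. Outcomes run to 12 months. No section says how an event after the last session, or a reaction that stops attendance, reaches the sheet. Session counts can differ fourfold between patients (8/2 = 4). That is a contrast between patients, and nothing in the article shows that it differs by arm.

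**5. Could other measures fill the gap?** Partly. GROC at six weeks can register worsening, and NPRS, PSFS and EQ-5D run to 12 months. The DN4 covers pins and needles and reduced sensation. Sensation, power and reflexes are tested at six and 12 months, but no baseline for these is named, so a new deficit may not be identifiable. None of these measures records an event with its onset, duration or care sought.

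**6. Size, with assumed capture rates.** Observed risk ratio = true risk ratio × (capture with neural mobilisation / capture with usual care). With a true ratio of 1:

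| Capture, neural mobilisation | Capture, usual care | Observed ratio |
|---|---|---|
| 90% | 60% | 1.5 |
| 60% | 90% | 0.67 |
| 80% | 80% | 1.0 |

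The ratio does not depend on the true rate.

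Equal under-capture leaves the ratio at 1 but weakens reassurance. If no events are recorded, the exact one-sided 95% upper limit is 1 − 0.05^(1/n): 8.4% for n = 34 and 4.3% for n = 68, if capture is complete. At an assumed 60% capture, the limits on the true rate become 8.4/0.6 = 14% and 4.3/0.6 = 7%.

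**The case against.** The case on the other side has real force.

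- **A reader might infer that the sheets are the sole source of harm data.** The article lists uses of the sheets and does not exclude others. It is a condensed account, and a full protocol may add adverse event forms or follow-up questions. This stands: the supportable statement is that the sheets are the only source stated. What remains is that the article does fix a source and a scope, and that the two sections differ on scope.
- **A reader might infer that events after the last session are always lost.** The article does not say so. The sheets are collected late, and nothing forbids a later entry. The measures in step 5 would also show some worsening. This stands too. The gap is the absence of any stated route for recording such events.
- **A reader might infer that the comparison of harm is biased.** No such comparison is planned, and the documents fix neither the direction nor the size of any distortion. What they support is a risk of under-capture and differential attribution.
- **The recording rule is not given.** The sentence is passive. It does not say that therapists write down only what they judge to be caused by treatment. The filter may be applied later, but it would still be applied to notes made by a person who knows the arm.
- **Therapists delivering manual treatment cannot be blinded.** This is true, and it is the reason to use the blinded contact as well. Harm questions on that call could, however, reveal the arm to the assessor. That cost is real and shapes the fix.

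**Conclusion.** The point holds as a weakness in how harm is ascertained. Someone following the article as written would collect harm data through therapists who know the allocation and screen for treatment-caused events. There is no stated route for later events or for reactions that end attendance, and blinded contacts that already exist carry no harm item. Such data would not support an unbiased reading of harm by arm.

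Direction and size are unknown. The ratios of 0.67 to 1.5 rest wholly on assumed capture rates and show only what unequal capture can do. The conclusion assumes that no fuller document adds adverse event questions at follow-up; if one does, only the mismatch in scope between Randomisation and Intervention remains. The primary efficacy analysis and the sample size of 102 are unaffected. This is a cheap improvement to the plan and not a threat to its main result.

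**What to change.** 1. Reconcile the Randomisation and Intervention sections on which adverse events are recorded. This concerns recording only; the referral rule is for the investigators.
2. Add one short question set to the blinded telephone calls at three and six weeks. Ask for new or worse symptoms since the last contact (such as arm pain, numbness, pins and needles, weakness, headache or dizziness), how long they lasted and whether care was sought. Record events regardless of presumed cause and use the same wording in both arms.
3. Place the set after all efficacy items, so that it cannot colour those answers. Word it so that it does not ask what treatment was given.
4. Repeat it at six and 12 months.
5. Keep the therapist sheets as a second source. Report both sources separately by arm, per patient over a fixed six-week window.

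The cost is about two minutes per existing contact (an estimate) and one form page, with no extra staff or visits. There are two downsides: more minor, non-specific events will be recorded in both arms, and there is a small risk that a patient's answer reveals the arm to the assessor.
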